**Protocol Version History:**

|               |           |
|---------------|-----------|
| Protocol V1.0 | 20Aug2019 |
| Protocol V2.0 | 04Mar2020 |
| Protocol V3.0 | 28Sep2020 |
| Protocol V4.0 | 05May2021 |
| Protocol V4.1 | 08Jun2021 |
| Protocol V5.1 | 18Aug2021 |
| Protocol V6.0 | 27Jan2022 |
| Protocol V7.0 | 19Aug2022 |
| Protocol V8.1 | 10Feb2023 |
| Protocol V9.0 | 10Oct2023 |
| Protocol V9.1 | 18Dec2023 |

## LIST OF ACRONYMS, ABBREVIATIONS, AND DEFINITION OF TERMS

|       |                                                                                                                       |
|-------|-----------------------------------------------------------------------------------------------------------------------|
| ACD   | acid-citrate-dextrose                                                                                                 |
| AE    | adverse event                                                                                                         |
| ALC   | absolute lymphocyte count                                                                                             |
| ALL   | acute lymphoblastic leukemia                                                                                          |
| ALT   | alanine aminotransferase                                                                                              |
| ANC   | absolute neutrophil count                                                                                             |
| BUN   | blood urea nitrogen                                                                                                   |
| CAR   | chimeric antigen receptor                                                                                             |
| CFR   | Code of Federal Regulations                                                                                           |
| CNS   | central nervous system                                                                                                |
| CR    | complete response                                                                                                     |
| CRF   | Case Report Form                                                                                                      |
| CRS   | cytokine release syndrome                                                                                             |
| CSF   | cerebrospinal fluid                                                                                                   |
| CSL   | Correlative Sciences Laboratory                                                                                       |
| CTEP  | Cancer Therapy Evaluation Program                                                                                     |
| DIPG  | diffuse intrinsic pontine glioma                                                                                      |
| DL    | dose level                                                                                                            |
| DLT   | dose-limiting toxicity                                                                                                |
| DMG   | Diffuse Midline Glioma, H3 K27M-mutant                                                                                |
| DR    | Dose Regimen                                                                                                          |
| DSMB  | Data Safety Monitoring Board                                                                                          |
| FDA   | Food and Drug Administration                                                                                          |
| GBM   | Glioblastoma                                                                                                          |
| GCP   | Good Clinical Practice                                                                                                |
| GMP   | Good Manufacturing Practice                                                                                           |
| HIPAA | Health Insurance Portability and Accountability Act                                                                   |
| HIV   | human immunodeficiency virus                                                                                          |
| IBC   | Institutional Biosafety Committee                                                                                     |
| ICF   | informed consent form                                                                                                 |
| ICH   | International Conference on Harmonisation of Technical Requirements for Registration of Pharmaceuticals for Human Use |
| IEC   | Institutional Ethics Committee                                                                                        |
| IND   | Investigational New Drug (application)                                                                                |
| IR    | incomplete response                                                                                                   |
| IRB   | Institutional Review Board                                                                                            |

|       |                                                |
|-------|------------------------------------------------|
| IV    | Intravenous                                    |
| MRI   | magnetic resonance imaging                     |
| MTDR  | Maximum tolerated Dose Regimen                 |
| NCI   | National Cancer Institute                      |
| CTCAE | Common Terminology Criteria for Adverse Events |
| NRM   | non-relapse mortality                          |
| OS    | overall survival                               |
| PB    | peripheral                                     |
| PCR   | polymerase chain reaction                      |
| PD    | progressive disease                            |
| PFNS  | preservative-free normal saline                |
| PFS   | progression-free survival                      |
| PI    | principal investigator                         |
| PR    | partial response                               |
| RCL   | replication-competent lentivirus               |
| RP2DR | recommended Phase 2 dose regimen               |
| SAE   | serious adverse event                          |
| SCRI  | Seattle Children's Research Institute          |
| TCPC  | therapeutic cell production core               |
| ULN   | upper limit of normal                          |
| US    | United States                                  |
| VS    | vital signs                                    |

## Definition of Terms

Investigational Product is defined as, “A pharmaceutical form of an active ingredient or placebo being tested or used as a reference in a clinical trial, including a product with a marketing authorization when used or assembled (formulated or packaged) in a way different from the approved form, or when used for an unapproved indication, or when used to gain further information about an approved use” [from International Conference on Harmonization (ICH) of Technical Requirements for Registration of Pharmaceuticals for Human Use Harmonized Tripartite Guideline E6: Guideline for Good Clinical Practice].

The terms “Investigational Product” and “study drug” may be used interchangeably in the protocol.

## ABSTRACT

This is a Phase 1 study of central nervous system (CNS) locoregional adoptive therapy with autologous CD4+ and CD8+ T cells that are lentivirally transduced to express a B7-H3-specific chimeric antigen receptor (CAR) and EGFRt. CAR T cells are delivered via an indwelling catheter into the tumor cavity or ventricular system in children and young adults with diffuse intrinsic pontine glioma (DIPG), diffuse midline glioma (DMG), and recurrent or refractory CNS tumors. Depending on the location of the tumor and the existence of metastatic (including leptomeningeal) disease, subjects will have CAR T cells delivered into the tumor cavity or the ventricular system. The primary objectives of this protocol are to evaluate the feasibility, safety, and tolerability of CNS-delivered fractionated B7-H3 CAR T cell infusions employing intra-patient dose escalation and to define the Maximally Tolerated Dose (MTD) and Recommended Phase 2 Dose Regimen (RP2DR) of CNS-delivered fractionated B7-H3 CAR T cell infusions through a modified 3+3 design and an expansion cohort. The secondary objectives are to assess B7-H3 CAR T cell distribution within the cerebrospinal fluid (CSF) and the extent to which B7-H3 CAR T cells egress into the peripheral circulation, and disease response to B7-H3 CAR T cells. The exploratory objectives are to describe B7-H3 expression in tumor tissue and/or normal tissue if a tissue biopsy, tumor biopsy, or resection is available; to describe the presence of B7-H3 CAR T cells in tumor tissue and/or normal tissue if a tissue biopsy, tumor biopsy, or resection is clinically indicated post-treatment; and to analyze blood, CSF, and tumor tissue for biomarkers of anti-tumor B7-H3 CAR T cell expression, safety, and activity.

## EXPERIMENTAL DESIGN SCHEMA

[figure not shown]

█ [REDACTED]

█ [REDACTED]

## **2 STUDY OBJECTIVES**

### **2.1 Primary Objectives**

- To assess the feasibility of CNS locoregional adoptive therapy with autologous CD4+ and CD8+ T cells lentivirally transduced to express a B7-H3-specific CAR EGFRt and a methotrexate resistant human dihydrofolate reductase mutein, delivered by an indwelling catheter into the tumor cavity or ventricular system in children and young adults with DIPG, DMG, or recurrent/refractory CNS tumors.
- To assess the safety of CNS locoregional adoptive therapy with autologous CD4+ and CD8+ T cells lentivirally transduced to express a B7-H3-specific CAR, EGFRt and a methotrexate resistant human dihydrofolate reductase mutein, delivered by an indwelling catheter into the tumor cavity or ventricular system in children and young adults with DIPG, DMG, or recurrent/refractory CNS tumors.
- To establish the tolerability of a fractionated CNS-delivered B7-H3 CAR T cell infusion schedule employing intra-subject dose escalation in children and young adults with DIPG, DMG, or recurrent/refractory CNS tumors.
- To define the maximally tolerated dose (MTD) and recommended Phase 2 dose regimen (RP2DR) of CNS-delivered fractionated B7-H3 CAR T cell infusions.

### **2.2 Secondary Objectives**

- To assess B7-H3 CAR T cell distribution within the cerebrospinal fluid (CSF) and the extent to which B7-H3 CAR T cells egress into the peripheral circulation.
- To assess disease response to B7-H3 CAR T cell locoregional therapy in children and young adults with DIPG, DMG, or recurrent/refractory CNS tumors.

### **2.3 Exploratory Objectives**

- To evaluate for presence of B7-H3 CAR T cells in tumor tissue and/or normal tissue if a tissue biopsy, tumor biopsy, or resection is clinically indicated post-treatment.
- To evaluate B7-H3 expression in tumor tissue and/or normal tissue if a tissue biopsy, tumor biopsy, or resection is available.
- To analyze blood, CSF, and tumor tissue for biomarkers of anti-tumor B7-H3 CAR T cell expression, safety, and activity.

### **3 ENROLLMENT AND ELIGIBILITY**

#### **3.1 Enrollment**

Upon consent for participation in a Seattle Children's Therapeutics immunotherapy clinical trial, subject demographic information is entered into the Immunotherapy Registration Portal and a unique Registration ID is appointed. Subjects are then transferred to the study-specific database where they are assigned a unique Study ID. Screening and eligibility information will be entered into the study-specific database where it will be reviewed by the Study Chair or their designee who will subsequently approve/deny subject enrollment to the study (consult the sponsor and/or case report form (CRF) Completion Guidelines for instructions related to the study-specific databases).

#### **3.2 Eligibility**

##### **3.2.1 Inclusion criteria**

1. Subjects must be age  $\geq 1$  and  $\leq 26$  years (except for the first 3 subjects, who will be enrolled in Arm A or Arm B and must be age  $\geq 15$  and  $\leq 26$  years) (this requirement has been met as of 8/27/2020).
2. Subject disease classified as one of the following:
  - a. DIPG at any timepoint following completion of standard radiotherapy
  - b. DMG at any timepoint following completion of standard radiotherapy
  - c. Evidence of refractory or recurrent CNS disease for which there is no standard therapy, defined by either of the following (further categorization by disease type is listed in Appendix 5 –Refractory and Recurrent Disease Categorization):
    - i. Recurrent disease (e.g., new site(s) of measurable or evaluable disease by radiographic imaging or histologic confirmation following completion of standard of care first-line therapy for which curative salvage therapy is not available or amenable), OR
    - ii. Refractory disease (e.g., measurable or evaluable disease that persists following completion of standard of care first-line therapy for which curative salvage therapy is not available or amenable)
3. Able to tolerate apheresis or already has an apheresis product available for use in manufacturing
4. CNS reservoir catheter, such as an Ommaya or Rickham catheter, present in the proper location for CNS-directed therapy delivered as specified for BrainChild-03
5. Life expectancy  $\geq 8$  weeks
6. Lansky or Karnofsky score  $\geq 60$ . Subjects who are unable to walk because of paralysis, but who are up in a wheelchair, will be considered ambulatory for purposes of assessing performance status

7. If subject does not have a previously obtained apheresis product that is acceptable and available for manufacturing of CAR T cells, subject must discontinue all anticancer agents and radiotherapy and, in the opinion of the investigator, have fully recovered from significant acute toxic effects of the following:
  - a. *Cytotoxic chemotherapy/biologic therapy*: All cytotoxic chemotherapy/biologic therapy must be discontinued  $\geq 7$  days prior to enrollment.
  - b. *Antibody Therapy*: The last dose of anti-tumor antibody therapy (including checkpoint inhibitor) must be at least 3 half-lives or 30 days, whichever is shorter, from the time of enrollment. Bevacizumab will be considered biologic therapy.
  - c. *Cellular Therapy*: must be at least 30 days from most recent cell infusion prior to enrollment
  - d. *Steroid use*: All systemically administered (i.e. Subcutaneous, Intramuscular, PO or IV) corticosteroid therapy (unless physiologic replacement dosing) must be stable or decreasing for  $\geq 1$  week prior to enrollment, with a maximum dexamethasone dose of 2.5 mg/m^2/day ongoing at enrollment. Corticosteroid physiologic replacement therapy for management of pituitary/adrenal axis insufficiency and/or topical administration (e.g. inhaled or dermatologic) is allowed.
8. Adequate hematologic values, all of the following in Table 3-1 must be true:

**Table 3-1 Screening Hematologic Values**

| Analyte                                      | Value                      |
|----------------------------------------------|----------------------------|
| Absolute lymphocyte count (ALC)  | $\geq 100$ cells/uL        |
| Absolute neutrophil count (ANC)              | $\geq 500$ cells/uL        |
| Hemoglobin                       | $\geq 9$ g/dL              |
| Platelets                        | $\geq 100,000/\mu\text{L}$ |

Value not required to be met if subject has previously obtained apheresis product acceptable and available for manufacturing of CAR T cells

Subjects receiving blood product transfusion(s) are acceptable as long as they are not determined to be transfusion refractory

9. Adequate renal function, as indicated by serum creatinine  $\leq$  the upper limit of normal (ULN), per Table 3-2:

**Table 3-2 Serum Creatinine ULN Based on Age and Sex**

| Serum Creatinine (mg/dL) ULN |      |        |
|------------------------------|------|--------|
| Age                          | Male | Female |
| 1 to < 2 yrs                 | 0.6  | 0.6    |
| 2 to < 6 yrs                 | 0.8  | 0.8    |
| 6 to <10 yrs                 | 1    | 1      |
| 10 to < 13 yrs               | 1.2  | 1.2    |
| 13 to < 16 yrs               | 1.5  | 1.4    |

|               |     |     |
|---------------|-----|-----|
| $\geq 16$ yrs | 1.7 | 1.4 |
|---------------|-----|-----|

10. Adequate hepatic function as indicated by either of the following:
  - a. Total bilirubin < 3 times ULN for age, OR
  - b. Conjugated bilirubin < 2 mg/dL
11. Adequate respiratory function as indicated by BOTH of the following:
  - a. Oxygen saturation  $\geq 90\%$  on room air without supplemental oxygen or mechanical ventilation, AND
  - b. No dyspnea at rest
12. Adequate neurologic function as indicated by all of the following:
  - a. Signs and symptoms of neurologic deficit must be stable for  $\geq 1$  week prior to enrollment, AND
  - b.  $\leq$  two anti-epileptic agents are required to control seizure activity, AND
  - c. No clinically evident encephalopathy present
13. Virology negative within 3 months prior to enrollment, to include all of the following:
  - a. HIV antigen & antibody, AND
  - b. Hepatitis B surface antigen, AND
  - c. Hepatitis C antibody OR if antibody positive, Hepatitis C polymerase chain reaction (PCR) is negative
14. Subjects of childbearing/fathering potential must agree to use highly effective contraception (Appendix 6 – Highly Effective Contraception) from the time of enrollment through 12 months following the last T cell infusion

### 3.2.2 Exclusion criteria

1. Presence of  $\geq$  Grade 3 cardiac dysfunction or symptomatic arrhythmia requiring intervention
2. Presence of primary immunodeficiency/bone marrow failure syndrome
3. Presence of clinical and/or radiographic evidence of impending herniation
4. For Arm C subjects only: Presence of > Grade 3 dysphagia
5. Presence of active malignancy other than the CNS tumor under study
6. Presence of active severe infection, defined as either of the following:
  - a. Positive blood culture within 48 hours of enrollment, OR
  - b. Fever > 38.2°C AND clinical signs of infection within 48 hours of enrollment
7. Pregnant or breastfeeding
8. Subject and/or authorized legal representative unwilling to provide consent/assent for study participation, including participation in the 15-year follow-up period, which is required if CAR T cell therapy is administered

9. Presence of any condition that, in the opinion of the investigator, would prohibit the subject from undergoing treatment under this protocol

## **4 DRUG INFORMATION**

### **4.1 T Cell Product**

Investigational product for BrainChild-03 is composed of autologous CD4+ and CD8+ T cells that express an B7-H3-specific CAR and EGFRt. The B7-H3-specific CAR consists of a scFv binding domain derived from the B7-H3-binding monoclonal antibody huBRCA84D. The CAR's signaling domains include 4-1BB and CD3ζ chain.

T cell product manufacturing will be conducted in the SCRI Therapeutic Cell Production Core (TCPC) GMP facility under approved Investigational New Drug (IND) processes. Cryopreserved cells will be stored in vapor phase in a controlled access LN2 (liquid nitrogen) freezer until released for clinical use. On the day of T cell product infusion, cryopreserved unit(s) will be thawed, aseptically washed, and formulated in a sterile, single-use syringe as specified in standard thaw and wash procedures. Formulated CAR T cell product must be administered prior to the expiration date/time specified in standard thaw and wash procedures and recorded on the syringe label.

#### **4.1.1 Possible side effects of intracranially delivered CAR T cell therapy**

Please see the SCRI-CARB7H3(s) Investigator's Brochure for safety information.

## 5 TREATMENT PROGRAM

### 5.1 Overview of Treatment Plan

#### 5.1.1 Treatment Arm assignment

Subjects will be enrolled into one of three Treatment Arms according to disease pathology, disease location, and subsequent CNS-directed CAR T cell delivery route.

**Arm A** will include subjects whose CAR T cells will be delivered into the tumor cavity.

**Arm B** will include subjects whose CAR T cells will be delivered into the ventricular system.

**Arm C** will include subjects with DIPG whose CAR T cells will be delivered into the ventricular system.

Within each Arm, subjects will be enrolled into a defined Dose Regimen (DR). Subjects will receive a different combination of Dose Levels (DL) depending on the DR into which they are enrolled.

The specific DLs within each DR are:

**Table 5-1 CAR T Cell Dose Levels**

| Dose Level (DL)  | Dose                        |
|------------------|-----------------------------|
| DL 1 (test dose) | 1 x 10  cells   |
| DL 2             | 2.5 x 10  cells |
| DL 3             | 5 x 10  cells   |
| DL 4             | 10 x 10  cells  |

During the time from apheresis to infusion of CAR T cells, subjects may return to the care of their primary physician and may receive additional cancer-directed therapy (see 5.4 Bridging Therapy). The site team will be notified when the subject's CAR T cell product is released and available so that the CAR T cell infusion may be scheduled.

CAR T cell therapy will be administered on Study Weeks 1 through 3 (Arms A and B) or Weeks 1 and 3 (Arm C) of each 4-week Course. Dosing will start with a test dose (DL 1) at Week 1. Arm A and B, DR 1 will establish the safety of the test dose plus a single DL escalation. Arm C DR 1 will establish the safety of the intermittent administration of the test dose without DL escalation.

#### 5.1.2 Dose Regimen assignment

Detailed rules for DR assignment are described in Section 9.9.1 Arms and DLT observation periods.

If the quantity of the initial manufactured CAR T cell product is less than the specified DL, but is otherwise releasable by TCPC, it may be administered as long as the subject meets criteria to

undergo initial T cell infusion (Section 5.5.1 Requirements for initial CAR T cell infusion) and the occurrence is clearly documented in the subject files (see [Section 5.6 Guidelines for Administering the CAR T Cell Product](#)). However, in the absence of a DLT during Courses 1 and 2, such subjects will not be evaluable for DR escalation per Section 9.9.2 Dose Regimen (DR) escalation rules.

If a subject has a releasable CAR T cell product but treatment is suspended (during the mandated period between participants, or while the data are under review by the Data Safety Monitoring Board [DSMB] or Food and Drug Administration [FDA]) and the subject is not medically stable enough to wait until treatment is reinitiated, the subject may receive their CAR T cell product according to the schedule and specific CAR T cell DLs of the maximum DR already deemed tolerable.

Subjects who are removed/withdraw from the protocol prior to receiving CAR T cell product will be replaced to meet statistical guidelines for evaluation of toxicity and feasibility.

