### **5.6 Guidelines for Administering the CAR T Cell Product**

The administered dose of CAR T cell therapy may be within  $\pm 10\%$  of the protocol prescribed dose. Administering a dose of CAR T cell therapy varying by greater than  $\pm 10\%$  of the protocol prescribed dose is not permitted without prior Sponsor approval. All dosing deviances should be communicated to the Sponsor and the occurrence clearly documented in the subject files. Please refer to [Section 5.1 Overview of Treatment Plan](#) for full details of the study dosing requirement.

Subjects may undergo CAR T cell infusion in the outpatient or inpatient setting. When clinically prudent, subjects may be admitted to the hospital following the CAR T cell infusion for observation and monitoring if they exhibit minor symptoms which, if to worsen, could place the subject at risk of an adverse medical outcome.

In addition to institutional guidelines for infusion of cellular products, subjects are to be administered CAR T cell product according to the following guidelines:

- Prior to CAR T cell product administration (in instances of documented allergy or sensitivity to any of the below pre-medications clinical discretion may be used for appropriate substitution):
  - Required: acetaminophen
    - Recommended dosing: 12.5 mg/kg (maximum dose 650 mg), PO
  - Optional: diphenhydramine
    - Recommended dosing: 0.5 mg/kg (maximum dose 50 mg), IV or PO
  - Optional: ondansetron
    - Recommended dosing: 0.15 mg/kg (maximum dose 8 mg), IV or PO
- Thawed, formulated CAR T cell product will be administered slowly through a catheter placed into the tumor cavity or ventricular system.
- Microaggregate filters and leukodepletion filters must not be used to infuse CAR T cell products.
- CAR T cell infusion must be followed by a preservative-free normal saline (PFNS) flush delivered slowly via a manual push technique to clear the administration line and catheter. The volume of PFNS is dependent on catheter size and will be determined at time of enrollment and then kept consistent for each CAR T cell infusion the subject receives.

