### **9.9.2 Dose Regimen (DR) escalation rules**

A subject will be considered DR escalation-evaluable if they are evaluable for MTDR DLT and are counted as part of a 3-subject dose escalation Cohort according to the rules described below.

The following rules will be applied separately and independently for each Arm. DLTs are defined in Section 5.2.

*Dose escalation rules using a modified 3 + 3 design for Arms A, B, and C.* DRs are detailed in Section 5.1.3.

1. Escalation and de-escalation decisions will use cohorts of 3 consecutive toxicity-evaluable subjects treated at the same DR
2. The dose escalation route will be similar to a 3+3 design, and will allow expansion on the tentative MTDR if 1 DLTs out of the first cohort of 3 and 1 DLTs out of the second cohort of 3 were observed
  - a. If 0 DLTs out of the first cohort of 3 (0/3) within a DR, and there is a DR available for escalation, it will escalate to the next DR. If there is no DR

available for escalation, then this DR is considered as tentative MTDR and another cohort of 3 will be treated at the current DR.

- b. If 1 DLTs out of the first cohort of 3 (1/3), a second cohort of 3 will be treated and evaluated at the current DR
  - i. If 0 DLTs out of the second 3 and there is a DR available for escalation, it will escalate to the next DR. If there is no DR available for escalation (1 DLT in first 6), the MTDR will be estimated
  - ii. If 1 DLTs out of the second cohort of 3 (i.e. 2 DLT in the first 6), a third cohort of 3 will be treated at the current DR. If there are 0 DLTs in the third cohort of 3, the MTDR will be estimated. If there is 1 DLT in the third cohort (i.e. 3 DLTs in the first 9), a final cohort of 3 will be treated at the current DR and the MTDR will be estimated once all subjects have been evaluated.
- c. If 2 or more DLTs out of any cohort of 3 ( $\geq 2/3$ ) toxicity-evaluable subjects, the current DR will be shut down and the DR will de-escalate to the previous DR. If the first 2 subjects of any cohort of 3 both experience DLTs and the third subject has not received CAR T cells, stop the cohort at 2 subjects and de-escalate to previous DR and the third subject will become the first subject of a new cohort. If there is no DR available for de-escalation (lowest), the arm will be shut down.

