| Amendment 11 | V9.0/2023.10.10 | 2023-12-01 | Addition of tumor inflammation-associated neurotoxicity (TIAN) definition, the timing of                                                                                                                                                                                                                                                                                                                                                                                                                                                                                                                                                                                                                                                                                                                                                                                                                                                                    |

|              |                 |  |                                                                                                                                                                                                                                                           |
|--------------|-----------------|--|-----------------------------------------------------------------------------------------------------------------------------------------------------------------------------------------------------------------------------------------------------------|
|              |                 |  | on study disease evaluation MRIs was updated to as clinically indicated, and the administered dose of CAR T-cell therapy may be within +/- 10% of the protocol prescribed dose. Update to Sponsor medical officer and minor other administrative changes. |
| Amendment 12 | V9.1/2023.12.18 |  | Amended to transition the role of Study Chair from [name] to [name] and to update the SCTx Sponsor representative to [name].                                                                                                     |

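### A product shortfall of any size makes a DLT-free subject non-evaluable for escalation (5.1.2), even where the dose stays within the 10% tolerance of 5.6, so the counted DLT rate is biased upward by a probably small amount

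*Protocol*

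**What the plan says.** Section 5.1.2 sets the trigger: "If the quantity of the initial manufactured CAR T cell product is less than the specified DL, but is otherwise releasable by TCPC". Such a product may be given if the subject meets the infusion criteria and the event is documented, with a reference to 5.6. The consequence is that "in the absence of a DLT during Courses 1 and 2, such subjects will not be evaluable for DR escalation", and 5.1.2 attributes this to 9.9.2. A subject with the same shortfall and a DLT is not excluded.

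Section 5.6 opens "The administered dose of CAR T cell therapy may be within" ±10% of the prescribed dose; variation beyond ±10% "of the protocol prescribed dose is not permitted without prior Sponsor approval". The version history dates this tolerance to V9.0.

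Section 9.9.2 has no product-quantity condition: "A subject will be considered DR escalation-evaluable if they are evaluable for MTDR DLT and are counted as part of a 3-subject dose escalation Cohort". Its decision unit is also stated without one: "Escalation and de-escalation decisions will use cohorts of 3 consecutive toxicity-evaluable subjects treated at the same DR".

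Section 9.5 provides replacement for subjects who leave study or die early. Section 9.9.1 requires all three subjects to have had at least one maximally intended dose in Course 2 before the next dose regimen (DR) opens. Neither says whether a dose slightly under nominal qualifies.

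**The concern.** A product at 90% to just under 100% of the DL can give a dose that 5.6 accepts, yet it falls below the DL for the purposes of 5.1.2. For a subject in that band, entry into the escalation count depends on the outcome being counted: a DLT puts the subject in, and its absence takes the subject out. Selection of this kind raises the DLT rate among counted subjects above the true rate.

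That rate drives the 3+3 decisions and the choice of the maximum tolerated dose regimen (MTDR), a primary objective. Each uncounted DLT-free subject also means another must be treated to complete a cohort of three evaluable subjects, within total accrual of up to 90 (9.1). Section 5.1.2 does not itself order replacement in this case; it follows from the cohort rule in 9.9.2.

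**Working it through.** **Is the conflict resolved elsewhere?**

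- 9.9.2, the section 5.1.2 relies on, contains no quantity rule.
- 9.5 deals with early removal or death, not with a subject who completes Course 2.
- 9.7 refers back to 9.5 and 9.9.1.
- 9.9.1 leaves the maximally intended dose without a tolerance.

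None of these reconciles 5.1.2 with 5.6.

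**Inputs.** The protocol gives no figure for this rule, so there is none to reproduce. Let p be the true DLT probability over Courses 1 and 2. Let q be the share of treated subjects whose initial product falls short but whose doses stay within the 5.6 tolerance. Both are assumptions. DLT risk is taken to be the same inside and outside the band, since the shortfall is under 10%.

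**Formula.** Every DLT counts; a DLT-free subject counts with probability 1 − q. The counted rate is

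p* = p / [p + (1 − p)(1 − q)].

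Per 100 treated subjects at p = 20% and q = 10%, all 20 DLTs count. Of the 80 DLT-free subjects, 8 are excluded and 72 count. The rate is 20/92 = 21.7%.

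From rules 2a and 2b(i) of 9.9.2, where a higher DR exists:

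P(escalate) = (1 − p*)³ + 3p*(1 − p*)⁵.

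With t = 3p*²(1 − p*) + p*³ for two or more DLTs in a cohort of three:

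P(DR closed in cohort 1 or 2) = t + 3p*(1 − p*)² t.

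At p = 20%:

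| q | Counted rate | P(escalate) | P(closed, cohort 1 or 2) | Uncounted per 100 treated |
|---|---|---|---|---|
| 0 | 20/100 = 20.0% | 0.709 | 0.144 | 0 |
| 5% | 20/96 = 20.8% | 0.691 | 0.156 | 4 |
| 10% | 20/92 = 21.7% | 0.671 | 0.170 | 8 |
| 20% | 20/84 = 23.8% | 0.626 | 0.202 | 16 |

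At p = 30% the counted rate is 30/96.5 = 31.1%, 30/93 = 32.3% and 30/86 = 34.9% for q = 5%, 10% and 20%.

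A simulation of one million subjects at p = 20% and q = 20% gave 23.8%, matching the formula. If subjects within tolerance count whatever their outcome, p* = p and the q = 0 row applies.

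**The case against.** **The sections govern different quantities.** 5.1.2 is triggered by the amount of initial product, 5.6 by the dose administered. A subject with ample product and a slightly light syringe is not caught by 5.1.2. This stands. A reader might infer that correctly dosed subjects in general count only if they have a DLT; the text supports that only for the shortfall group.

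**The band may be nearly empty.** One product feeds several infusions. Over two courses, Arm A/B DR 1 needs 4 × 1 + 2 × 2.5 = 9 (× 10⁷ cells) and Arm C DR 1 needs 4 × 1 = 4 (× 10⁷). A total product just under one DL could not supply both courses without further manufacture. If the specified DL instead means the whole regimen, a per-dose tolerance is a different yardstick. This also stands, and it exposes a further gap: the term is undefined. The version history, explaining a change to the lymphocyte criterion, reports no manufacturing problems. That hints at a low q but gives no figure for it.

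**The convention is conservative.** Counting DLTs but not DLT-free courses after real underdosing is normal, and 9.5 does something similar for early leavers. This is accepted below the tolerance. It does not justify the same treatment of doses the protocol permits.

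**Sponsor approval.** A reader might infer that 5.1.2 allows on documentation alone what 5.6 allows only with approval. The documents do not support this: the same 5.1.2 sentence refers to 5.6, so the approval requirement carries over.

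**Conclusion.** The inconsistency is real on the literal text, and no other section resolves it. Within the limited group whose product shortfall leaves doses inside the 5.6 tolerance, inclusion depends on outcome and the counted DLT rate is biased upward for any q above zero. The bias is about 1 to 2 percentage points if q is 5–10%, nearly 4 points at a true risk of 20% if q is 20%, and nil if nobody falls in the band. It rests on an assumed q and on equal DLT risk inside and outside the band.

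The direction is cautious: less escalation, a possibly understated MTDR and some extra subjects treated. It does not expose subjects to a more toxic regimen.

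A reader might also conclude that the rule pushes a tolerable regimen over the 34% limit in 9.9.4, because the counted rate is 34.9% at p = 30% and q = 20%. That goes too far. Nothing supports a q that high, and 34.9% is an expected value, whereas 9.9.4 applies to observed fractions such as 2/6. The point deserves correction because it decides who enters a live escalation count and is cheap to settle, not because a large distortion has been shown.

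**What to change.** Reconcile 5.1.2 with 5.6, 9.5, 9.9.1 and 9.9.2:

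1. Keep the 5.1.2 trigger, a shortfall of the initial manufactured product, and state which DL or doses of the regimen the specified DL refers to.
2. Treat a subject as non-evaluable in the absence of a DLT only when the shortfall takes the dose below the lower limit of the 5.6 tolerance. Subjects within tolerance count with or without a DLT.
3. State in 9.5 and 9.9.1 that a dose within tolerance counts as a maximally intended dose, and put the evaluability rule in 9.9.2, where 5.1.2 already points.

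The exclusion should not be extended to any single infusion outside ±10%. That would remove DLT-free subjects who had sufficient product and are evaluable today, and could enlarge the outcome-dependent exclusion.

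The cost is a sentence in 5.1.2 with matching cross-references. No dose changes; only the counting does. The downside is that doses slightly below nominal are counted as that DL, which 5.6 already accepts.
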